### Research questions

1.2

•What are the group-average outcomes of the online intervention at the end of treatment and at a six-month follow-up?•How many individuals experience a reliable change when it comes to ADHD-symptoms and quality of life at the end of treatment and at a six-month follow-up?•Did the participants experience any negative consequences in relation to the online intervention?•How do participants who have discontinued treatment view the online intervention and their participation?•How do people who have undergone the entire treatment (≥ six modules) perceive the online intervention and their participation, both in terms of helping and hindering aspects?•What are the psychometric properties of the Swedish translation of ASRS in a Swedish population?

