#### Adult Attention-deficit/hyperactivity disorder Quality-of-Life scale (AAQoL)

2.5.1

The AAQoL (Brod et al., 2015; Brod et al., 2006) is a disease-specific quality of life measure for adults with ADHD. The instrument measures quality of life-consequences of ADHD in four domains using and consists of 29 items. The instrument has excellent internal consistency (Cronbach's α = 0.93 for the overall measure). One example of an item is “In the last two weeks, how hard has it been for you to remember important things?”, scored on a five-point Likert-like scale from “Not at all/Never” (1) to “Extremely/Very Often” (5). The scale ranges from 0 to 100. The sum of the AAQoL is one of the two main outcomes measures in the study.

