#### Adult ADHD Self-Report Scale-V1.1 (ASRS-V1.1) Symptoms Checklist (ASRS)

2.5.2

The ASRS is an instrument that measures ADHD-symptoms (Kessler et al., 2005). The instrument consists of 18 items that correspond to the 18 symptom-criteria for ADHD found in the DSM-IV-TR (Association, 2000). Of these 18 questions, six have been identified as most predictive of ADHD-symptoms. The overall range of the entire measure is 0 to 72. However, there are separate items focusing on attention and hyperactivity. The ASRS is the second main outcome measure of the study.

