### Statistical analysis

2.8

All outcomes will be analyzed using a series of ANOVAs, according to intent-to-treat-principle and missing values will be handled by using multiple imputation. Bonferroni-corrections to adjust for family-wise errors will also be used. The only exception applies to the NEQ which is only reported descriptively. Individual changes on the AAQoL and ASRS are determined using the Reliable Change Index (Jacobson and Truax, 1992; Maassen, 2004), i.e., yes/no, for improvement, deterioration, and non-response. For recovery, the Reliable Change Index and a positive change of two standard deviations in the direction of functionality will be used, i.e., criterion a (Jacobson and Truax, 1992). Given the large sample size that the study aims to recruit, moderation analyses are possible to conduct, but will be performed post hoc. Exploratory and confirmatory factor analyses will be used alongside reliability calculations (Omega) and analytic techniques used in Rasch analysis.

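### The recovery definition equates a two-SD change with criterion a, which is a post-treatment cut-off; the two rules are incompatible and the sentence should fix one

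*Protocol article*

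**What the plan says.** Section 2.8 sets out two layers of individual classification. First, "Individual changes on the AAQoL and ASRS are determined using the Reliable Change Index", which sorts participants into improvement, deterioration and non-response. Second, recovery adds a further condition: "the Reliable Change Index and a positive change of two standard deviations in the direction of functionality will be used, i.e., criterion a".

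The section does not say whose standard deviation is meant, gives no cut-off score, and explains criterion a only by this wording and a citation.

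For the AAQoL, section 2.5.1 reports a reliability: "The instrument has excellent internal consistency (Cronbach's α = 0.93 for the overall measure". For the ASRS, section 2.5.2 reports no reliability, only the score range: "The overall range of the entire measure is 0 to 72". Both scales are named as main outcome measures.

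The related research question in section 1.2 is "How many individuals experience a reliable change when it comes to ADHD-symptoms and quality of life at the end of treatment" and at six months. It asks about reliable change and does not mention recovery.

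**The concern.** The abbreviation that joins the two halves of the recovery sentence presents them as the same thing. They are not. A change of two SD compares a person with their own baseline. Criterion a compares the person's later score with a fixed point, two SD beyond the mean of the dysfunctional group.

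The usual logic of a two-part recovery rule is that the Index shows the change exceeds measurement error and the cut-off shows where the person has arrived. If the second part is also a change, and a much larger one, the first part does nothing and no part of the rule describes the end state.

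Recovery is the strongest individual-level statement the trial would make on its two main outcomes. As the sentence stands, one analyst could follow the words and another the label. Each could point to the text, and they would count largely different people. The choice could also be made after the data are seen.

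**Working it through.** The article states no recovery rate, Index threshold or cut-off, so there is no figure to reproduce. The check asks whether the two readings agree.

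**Inputs from the article.** AAQoL reliability 0.93 (2.5.1). ASRS reliability not given, so taken over a range of 0.70 to 0.95.

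**Assumptions.** Classical two-sided 95% Index; SD taken as the baseline SD; equal SD before and after; normal scores; pre-post correlation ρ of 0.5 or 0.7; mean gain g of 0 to 0.8 SD. Scores are oriented so that higher means better functioning.

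**Step 1: can the Index bind under the change rule?** In baseline SD units the Index threshold is 1.96 × √(2(1 − r)).

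- AAQoL, r = 0.93: 1.96 × √0.14 = 0.73 SD.
- ASRS, assumed r: 1.52 SD at 0.70, 1.24 SD at 0.80, 0.62 SD at 0.95.
- The threshold equals 2 SD when r = 1 − (2/1.96)²/2 = 0.48.

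Anyone who changes by 2 SD has therefore already passed the Index on the AAQoL, and on the ASRS at any reliability above about 0.48.

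**Step 2: do the rules pick the same people?** Two hypothetical participants, in baseline SD units from the baseline mean:

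- Start −1.5, end +0.6. Change 2.1: recovered by the change rule, but well short of the +2 cut-off.
- Start +0.9, end +2.1. Change 1.2, above 0.73, and beyond the cut-off: recovered by the cut-off plus Index, but not by the change rule.

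**Step 3: how often does this happen?** With baseline X and later score Y, the change Y − X has mean g and SD √(2(1 − ρ)).

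- Change rule: 1 − Φ((2 − g)/√(2(1 − ρ))). For ρ = 0.5 and g = 0.4 this is 1 − Φ(1.6) = 5.5%.
- Cut-off plus Index: P(Y ≥ 2 and Y − X > 0.73).
- Both: P(Y ≥ 2 and Y − X ≥ 2).

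Bivariate normal probabilities at r = 0.93:

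| ρ | g | Change rule | Cut-off + Index | Both | Change-rule cases short of cut-off | Cut-off + Index cases missed by change rule |
|---|---|---|---|---|---|---|
| 0.5 | 0 | 2.3% | 1.6% | 0.4% | 82% | 74% |
| 0.5 | 0.4 | 5.5% | 4.3% | 1.4% | 75% | 68% |
| 0.5 | 0.5 | 6.7% | 5.3% | 1.8% | 73% | 66% |
| 0.5 | 0.8 | 11.5% | 9.7% | 4.0% | 66% | 59% |
| 0.7 | 0 | 0.5% | 1.1% | 0.1% | 83% | 92% |
| 0.7 | 0.4 | 1.9% | 3.6% | 0.5% | 76% | 87% |
| 0.7 | 0.5 | 2.6% | 4.6% | 0.7% | 74% | 85% |
| 0.7 | 0.8 | 6.1% | 9.0% | 2.0% | 68% | 78% |

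At r = 0.80 the change-rule columns are unchanged, and the last column runs from 49% to 84%.

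**Step 4: does the Index work once the cut-off is used?** Yes. Of those beyond the cut-off, 15% to 51% fail the Index at r = 0.93, and 33% to 77% at r = 0.80.

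**The case against.** The best defence is that the sentence names criterion a and cites its source. Pairing it with the Index suggests that the standard two-part rule was meant and loosely paraphrased. An analyst who follows the label applies the cut-off, the Index then does its job, and nobody is misclassified. This stands as a limit on the claim. A reader might infer that the trial will label the wrong people as recovered, but that follows only if the literal words are applied. It does not remove the defect, because the text supports either choice.

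Three other strong readings are not supported:

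- **Wrong sign for the ASRS.** A positive change could look wrong on a scale where improvement is a fall. The same sentence specifies the direction of functionality, which settles the sign for each scale.
- **Recovered people remaining in the clinical range.** The article gives no norms or clinical range for either scale. The calculation shows only that many would not reach baseline mean plus two SD.
- **Main results at risk.** The ANOVAs do not use this rule. Improvement, deterioration and non-response rest on the Index alone, and the research question asks about reliable change.

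The size also deserves caution. The correlations and gains are assumed; the only effect size in the article is d = 0.1. If a mean gain of 0.1 SD is used, the rates are 2.9% against 2.1% (ρ = 0.5) or 0.7% against 1.5% (ρ = 0.7). With about 100 per arm, assuming equal allocation of 200, that is about one person per arm. Which rule gives the higher rate depends on the correlation. The high disagreement shares are fractions of small groups.

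Finally, a condensed article may leave the SD source to an analysis plan. That is fair for the detail, but the contradiction is in what the article does state.

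**Conclusion.** The point holds as a contradiction in a stated decision rule. Section 2.8 gives two incompatible definitions of recovery for both main outcomes. Under the literal one the Index is redundant for the AAQoL, and for the ASRS at any reliability above about 0.48, and the end state is ignored.

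At reliability 0.93, 66% to 83% of those recovered by the change rule fall short of the cut-off, and the change rule misses 59% to 92% of those who meet the cut-off plus the Index. The overall rates differ by 0.6 to 1.9 percentage points for gains up to 0.5 SD, and by up to 3.0 points at 0.8 SD.

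The redundancy result rests on the article's alpha, the classical Index and the baseline SD. The incompatibility rests on the standard meaning of criterion a, which the article does not spell out. The shares are illustrative.

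Because recovery is a secondary classification and the harm depends on which half of the sentence is followed, this is a should-fix point.

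**What to change.** Replace the two-SD change in section 2.8 with an end-state cut-off. Suggested wording:

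*A participant is classified as recovered if there is reliable improvement by the Reliable Change Index and the score at that assessment is at least two baseline SD beyond the baseline mean: at or above mean + 2 SD for the AAQoL, at or below mean − 2 SD for the ASRS. The mean and SD are those of the reference sample.*

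Name the reference sample; the pooled randomised sample at baseline is one reasonable choice. State the reliability used in the Index for each scale, since none is given for the ASRS.

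The cost is a sentence or two in the analysis section, settled before outcome data are examined. No data collection, sample size or group-level analysis changes.

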### Qualitative interviews and analysis

2.9

For the qualitative studies, participants are recruited based on either dropping out of treatment prematurely or completing the full online intervention. Recruitment is therefore based on participants sharing a specific set of experiences, i.e., critical cases. Thematic analysis will then be applied to explore recurrent themes in their accounts of undergoing treatment (Braun and Clarke, 2006, Braun and Clarke, 2013; Clarke et al., 2015).

## Discussion

3

The current protocol has described a clinical trial that will investigate the effect of iCBT for individuals with ADHD-symptoms who are either studying at a university or college, or of an adult working population. There is presently a lack of research that has explored the effects of psychological treatments for these particular groups. In addition, there are also few studies investigating the potential in disseminating online interventions for the type of difficulties often associated with symptoms of ADHD. The results from the current study will therefore provide useful knowledge on whether this support could be helpful for adults with ADHD. By combining measures of quality of life and symptoms of ADHD with measures of depression, anxiety and perceived stress, the current study will evaluate the effects of the program on both primary and secondary adult ADHD outcomes, including a six-month follow-up. Subscale scores on the AAQoL at baseline, post-treatment and follow-up could be explored to assess impairment and change in different life domains. There is also a possibility to explore the relationship between AAQoL and ASRS scores throughout the study process. Furthermore, the use of qualitative interviews will enable an investigation on the experiences of undergoing and completing iCBT for ADHD-symptoms, focusing on factors related to both dropout and completion of treatment, which in turn can be useful in developing more effective online interventions. Among the many strengths of the current study is the fact that the treatment will consist of several modules that the participants can choose from, which is believed to match their individual difficulties and settings better than a generic outline. In addition, the size of the sample is much larger compared to previous studies, which will allow more robust statistical inferences and subgroup analyses, as well as a psychometric evaluation of a common instrument for determining ADHD-symptoms. Furthermore, the use of a structured clinical interview to screen participants will provide a better overview of comorbidities among the included participants. Lastly, all of the researchers involved in the current study, as well as Psykologpartners W& W AB who manages the online intervention, have extensive experience of conducting research on iCBT. This contributes to, what we believe, a successful clinical trial in terms of recruitment, treatment delivery, and data collection and analysis. However, there are also a number of limitations that need to be addressed. The use of waitlist controls limits the conclusions that can be inferred from the treatment outcome but was deemed most appropriate given the use of an internet-based modality (i.e., providing a face-to-face treatment as a comparator was not feasible). Moreover, the relatively short follow-up period and the use of few measurement points could limit the inferences that are possible to make about changes during treatment and its long-term effects. However, due to the difficulties facing many individuals with ADHD-symptoms, such as inattention and restlessness, it was not considered possible to include additional measurement points than the ones included. To get the participants to answer the surveys at the pre-determined measure points reminders will be utilized and the therapists will reach out to those not responding in time. Similarly, there is also a risk that many of the participants will drop out from treatment. This will be managed by contacting participants that fail to complete the modules on a weekly basis and offering support in case problems arise. Further, the use of self-referrals in clinical trials always poses a problem since they might not accurately reflect the demographic composition of the target group. This can in turn result in selection bias, which limit the generalizations possible to make from the study. Comparisons to other research samples will therefore be made to understand whether the recruited participants differ in any sense and if this might have affected the results of treatment. Lastly, even though adherence can be monitored with regard to the number of modules completed, it is still difficult to determine the amount of time each participant spent on engaging with the content and the exercises included. The current study will however only be able to probe for this using self-reports and not objective data, which can be seen as a limitation. Furthermore, the fact that ASRS has not been validated in Swedish is a limitation. If the psychometric evaluation does not confirm the instrument's validity this might make it hard to interpret the results of the study. However, ASRS has been used in a several of studies with good results (Kenter et al., 2023; Moëll et al., 2015) and the instrument has been validated with good results in many different languages (Adler et al., 2019; Green et al., 2019; Vňuková et al., 2022; Yeh et al., 2008).

Another limitation is the inclusion criteria regarding university studies and/or employment might create a threshold that excludes individuals with more severe ADHD-symptoms that might have problems with maintaining employment or carrying out university studies. The consequence of this might be that the study fails to recruit a segment of individuals with ADHD that might benefit from treatment.

## Conclusion

4

The present study protocol has described a clinical trial of iCBT for individuals with symptoms of ADHD and is believed to increase the current understanding of how to provide psychological treatments for a particular group that typically receive very little support apart from pharmacotherapy. The aim is to provide an effective online intervention that might increase access for those who do not receive help, and could, if found beneficial, become an important addition to medication, increasing quality of life and managing symptoms of ADHD, anxiety, depression, and stress.
